#### 2.6.2. Whole-School Surveys

There are three surveys to be carried out by all students in the school. The whole-school survey is part of the feasibility study and is carried out through an online survey platform. It is a mandatory action to be carried out by the school and is carried out during the first two months of the academic year. The school uses this information for creating and implementing three school specific action plans. Within this survey there are details of participation levels and barriers to taking part in physical education and extra curriculum activities. Both staff and students complete a second survey halfway through the process with items also related to process evaluation. Items will test implementation, fidelity and satisfaction of the tasks completed to date. The final whole-school survey has items related to process evaluation and is completed towards the end of the academic year but before the accreditation visit. The survey will also be held on an online survey platform. Due to the difficulties in getting whole-school engagement towards the end of the school year, the survey has pragmatic evaluation items whereby it can be completed on a mobile device such as a tablet or smart phone. 

### 2.7. Sample Size

There are three schools that are part of the feasibility study. Unlike a sample size calculation, a justification is made for feasibility studies [53]. In Table 4, information about the size of the school, the type and the number of participants expected to complete the comprehensive arm of the study is presented. 

According to the Department of Education and Skills school lists, School B is one of the largest secondary level in Ireland, with 1313 enrolled students. It is also a DEIS school. Approximately 10% of secondary level students attend a DEIS designated school. Moreover, there are known socioeconomic barriers towards PA [6], therefore it is necessary to carry out this feasibility in a DEIS school environment. School A is an all-girls school. Almost one in five schools in the country are all-girls’ schools. There are many reports of girls having lower levels of PA than boys and therefore it is essential to include an all-girl’s school. School C has a slightly fewer number of students than the national average of 999 students per school. Moreover, the ratio between girls and boys is slightly higher for girls (1:1.05), whereas the national average in mixed schools tends to have fewer girls than boys (1:0.87). 

### 2.8. Data Analyses

#### 2.8.1. Quantitative Data

The data from the surveys are analysed through relevant statistical methods for the follow up data in this feasibility study. Compatible data between comprehensive and basic surveys can be used to determine the test-retest reliability of the items given that a smaller subsample of the entire school. As reliability is an important psychometric property for question items, this is carried out during the first phase of data collection. 

Students take part in the comprehensive study have their measures taken two times during the academic year. The first time takes place in autumn 2018 and the second takes place six months later during the spring 2019. Accelerometer data are transferred through the ActivPal software based on 15sec epoch. The standardised cut-offs for different types of motion; sleep, standing, light, moderate and vigorous PA are then compared at an individual level from pre- and post-test time points. Similarly, the height, weight and grip strength data is compared between the time points and used to control the differences in accelerometer data. Comprehensive survey data is also analysed with differences in PA and school related factors. 

Exploratory approaches include cross-sectional multivariate analyses of PA and school-related factors as independent variables and device-based PA and perceptions of PA opportunities as the dependent variables. Mixed models and multi-level regression analyses can be used on the data that has sufficient follow up data from the first time point. The multi-level approach takes into account between- and within- individual processes that explain variances in the outcome measures. Through this approach, it is possible to test the extent of PA (psychosocial variables) and school-related factors in relation to changes in PA levels and opportunities, at the same time to examine the individual versus the school factors that contribute to the outcome variables. 

The follow-up data adds another level of analysis that can test the changes through the intervention. It makes it possible to examine, for example, the changes in PA levels across the schools from the beginning and the end of the study, while also taking into account changes in the psychosocial variables included in this study. The interactions between the contexts can confirm behavioural change theories by examining the mediating and moderation mechanisms in PA levels. The majority of the statistical analysis would be carried out using IBM SPSS. 

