#### 2.2.2. Student Recruitment

In the participating schools, there are two levels of student engagement—basic and comprehensive. Although all students are exposed to the same SLASF programme, those engaged in the SLASF Basic are required to complete less data collection measures than those in the SLASF Comprehensive. The whole school is involved in the SLASF Basic and a random class from each year group is selected to take part in the SLASF Comprehensive. Classes are known as mixed ability tutor groups. Students obtain their consent to take part in the study. Even though there may be some students who do not obtain consent or would not like to withdraw from the comprehensive aspect of the study, there is no likely reason for them to influence the feasibility of the study. 

The SLASF initiative is structured to fit into the TY framework providing real and meaningful opportunities for student voice and youth leadership. A TY class would be nominated by the school as the SLASF TY class. This TY class attends classes in relation to SLASF tasks including youth leadership, mentoring and PA promotion. 

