A school census questionnaire was developed to help the SLASF team to identify their action plan. Core questions about PA opportunities, physical education, involvement in extra-curriculum activities and barriers to PA were included in an online survey. For a week after the awareness week, the survey is available for completion. All responses are anonymous and completed confidentially. Class teachers supervise and help answer any technical questions related to the completion of the survey. The data is stored on a secure server that is only accessible to the researchers. However, the overall results for each variable would be computed and provided for the school to carry out their own descriptive analyses with the TY group. The TY class can then produce meaningful findings from the survey to show the school through the notice board and used for one of the planned actions. 

For the TOW event a free rope and a 2 ½ h workshop will be provided for each school. This will enable TYs to coach and officiate TOW competitions and SLASF committee members that complete the course will receive a TOW Community Coach certificate upon completion. Each class in the school will be involved in this event with each having 3 TOW teams that compete against each other during tutor time or physical education class to decide what team will represent the class. Each class TOW team competes against the other classes in their year group during lunchtime to find the best TOW team for their year. Local role models can be invited to help launch the event by taking part in one of the TOW teams. This event should take place before the mid-autumn break. 

After the mid-autumn break, the schools would have access to their school’s results from the school questionnaire. The SLASF teams are given a month to review the results and start to design an SLASF action plan. At least three action points need to be agreed upon by the SLASF team. The proposed SLASF actions should be presented to the Principal for agreement. The agreed actions are then implemented in the second half of the school year. Towards the end of the year, the three agreed actions will be reviewed by the SLASF team members and presented to the school Principal during the last two weeks of the school year.

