#### 2.5.4. Questionnaires

There are two types of online surveys carried out throughout the year. The basic survey is completed by the entire school. This survey is anonymous and the focus is on PA participation and barriers to school related physical activities. This survey is a compulsory part of the SLASF process. Administration of the survey is decided by the school, with the intention to cover the entire school. Ideally, a census sweep of the school takes place at the same time. However, there may be some technical issues that may prevent this from happening. For example, schools may have a limited number of computers accessing the internet at any one time (bandwidth limits), may have a limited number of units to complete the survey (lack of tablets or computers) or could not get all the school to take part at the same time (timetabling issues). The results of the survey will be given back to the school for the purpose to plan specific school-based interventions. Therefore, it is important that the mode of data collection, analysis and reporting can be completed quickly and easily. Failing all technical capabilities to collect from an online platform, extra resources would be dedicated to ensure double coding from pen and paper surveys. 

The second type of survey is a comprehensive survey, used for evaluating the feasibility of the study. The participants in this study input their user-ID so that the data can be linked from the beginning and end of the year long programme. Completion of the online survey takes place as one of the testing stations during the data collection visits. All the students have tablets or allocated to a school computer to complete the online survey. Details of the instruments are reported in Table 3.

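### Test-retest reliability is planned between the basic and comprehensive surveys, but the basic survey is anonymous, so as described no student's two answers can be paired

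*Protocol article*

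**What the plan says.** Section 2.8.1 (Quantitative Data) states: "Compatible data between comprehensive and basic surveys can be used to determine the test-retest reliability of the items". The next sentence gives the timing: "As reliability is an important psychometric property for question items, this is carried out during the first phase of data collection".

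Two places describe how the whole-school survey handles identity. Section 2.5.4 (Questionnaires) says of the basic survey: "This survey is anonymous and the focus is on PA participation and barriers to school related physical activities". Section 2.5.2 (Activities for Certification) says of the school census questionnaire: "All responses are anonymous and completed confidentially". Both accounts describe a whole-school online survey whose results go back to the school for planning its actions, so they evidently concern the same instrument.

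The comprehensive survey is different. Section 2.5.4 says: "The participants in this study input their user-ID so that the data can be linked". The stated purpose is to join each student's beginning-of-year and end-of-year records.

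Section 2.2.2 (Student Recruitment) explains the overlap: "The whole school is involved in the SLASF Basic and a random class from each year group is selected" for the comprehensive part. The comprehensive students are therefore a subset of those who take the basic survey.

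**The concern.** Intraclass correlation, kappa and the test-retest correlation all use within-person pairs. The design puts the same students in both surveys, so the intention is sensible, but only one of the two records carries an identifier. If the basic survey is collected as stated, the pairs cannot be formed afterwards, because a missing key cannot be restored at the analysis stage.

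At stake is the psychometric check itself, which Section 2.8.1 calls important. The team would either be unable to report it or might report agreement between group distributions under the name of reliability.

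**Working it through.** The protocol article gives no reliability coefficient, target value or sample size for this analysis, so there is no stated figure to reproduce. Section 2.7 says of the sample as a whole: "Unlike a sample size calculation, a justification is made for feasibility studies". The check is one of record linkage.

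**1. What the analysis needs.** Two records per student on the same items, joined by a common key.

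**2. What each survey supplies.**

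| | Basic / census survey | Comprehensive survey |
|---|---|---|
| Who answers | Whole school (2.2.2, 2.5.4) | One random class per year group (2.2.2) |
| Identifier | None; anonymous (2.5.2, 2.5.4) | User-ID (2.5.4) |
| Stated use of identifier | Not applicable | Joining the beginning and end of the year |
| Consent | Passive (2.3) | Opt-in (2.3) |

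No section describes an ID, a self-generated code or any other key on the basic survey, either for the comprehensive classes or for anyone else.

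**3. Number of possible pairs.** From Table 4, intervention schools only, because Section 2.5.4 makes the basic survey a compulsory part of the SLASF process:

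- enrolled: 971 + 863 + 1313 = 3147
- expected in the comprehensive study: 100 + 150 + 150 = 400
- share: 400 / 3147 = 12.7%

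The 400 are the largest set in which test-retest pairs could exist. With no key on one of the two records, the number that can be paired by a documented identifier is 0.

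**4. Whether group data can stand in.** They cannot. As an illustration, assume a yes/no item answered yes by 50% on both surveys. Let *a* be the proportion answering yes both times. The margins force the proportion answering no both times to equal *a* as well, with *a* anywhere from 0 to 0.5.

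- observed agreement = 2*a*, from 0 to 1
- chance agreement = 0.5 × 0.5 + 0.5 × 0.5 = 0.5
- kappa = (2*a* − 0.5) / (1 − 0.5) = 4*a* − 1, from −1 to +1

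Identical group percentages are compatible with every value of kappa. The 50% is an assumption chosen to show the principle and is not a figure from this trial.

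**5. Whether the text could mean the autumn and spring waves.** Those waves are linked by user-ID, but Section 2.8.1 names the comprehensive and basic surveys and puts the work in the first phase. The two waves are also six months apart and span the programme, so they would not give a test-retest estimate.

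**The case against.** **The wording is permissive.** The first sentence in Section 2.8.1 only says what the data could be used for. This has little force, because the following sentence says the work is carried out and when.

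**A journal article condenses, and a linking code may appear in the full protocol.** That would be a good answer to a missing detail such as the choice of coefficient. Here the article asserts anonymity in two places and also asserts an analysis that needs identity. The conflict lies between statements that are present. It remains true that the zero applies only to the procedures described. A code for the subsample is conceivable, and so is matching on class, age and sex, but neither is mentioned and either would qualify the stated anonymity.

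**The analysis is ancillary.** This stands. The primary objective in Section 1.4 is acceptability, none of the stopping criteria in Table 1 uses a reliability coefficient, and the pre/post comparison of the comprehensive survey is linked by user-ID and unaffected.

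**Stronger readings that the documents do not support.** A reader might infer that the retest interval is left open and that the launch event could fall between the two surveys, mixing true change with unreliability. The visible text puts the census before the launch and the first comprehensive measures in autumn 2018, but Figure 1, the timeline of intervention and research components, is not reproduced in the text reviewed and may give the dates. A reader might also infer that the Integration stopping criterion is weakened because the items on physical activity opportunities would go untested. Table 3 lists the comprehensive battery. Section 2.5.2 says the census has core questions on opportunities, but nothing shows that these are the same items.

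**Conclusion.** The contradiction holds. Section 2.8.1 plans a within-person analysis across two surveys, and Sections 2.5.2 and 2.5.4 make one of them anonymous. As described, 0 of about 400 expected intervention-school students can be paired, and the group comparison that remains does not measure reliability.

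This rests on two readings: that the census questionnaire and the basic survey are the same instrument, and that no linking key exists beyond what the article describes. The 400 is the expected number in Table 4, not a count of students who consented or responded.

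It should be fixed, at moderate priority. The loss would be a secondary psychometric check, and no stop, revise or continue criterion in Table 1 uses it.

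**What to change.** Reconcile Section 2.8.1 with Sections 2.5.2 and 2.5.4 in one of three ways.

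1. **Add a key for the comprehensive students.** Those who opted in enter their user-ID, or a pseudonymous code, on the basic survey, and all other students stay anonymous. Compute the intraclass correlation or weighted kappa, as the item scale requires, on those pairs. The cost is one field on the online form, amended anonymity wording, an added line in the comprehensive information sheet and a submission to the ethics committee, which Section 2.10 foresees for important protocol changes. The downside is that these consenting students' basic survey becomes coded rather than anonymous.

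2. **Keep the basic survey anonymous and retest elsewhere.** Repeat the shared items within the ID-linked comprehensive survey after a short, stated interval. This costs some extra student time and leaves the anonymity statements untouched.

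3. **Delete the test-retest claim.** This costs nothing in data collection, but the check is lost.

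The first option works only if the field is in place before the basic survey is run.

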### 2.2. Recruitment

#### 2.2.1. School Recruitment

The SLASF programme is a comprehensive programme and employs a whole school approach. As an intervention programme, schools were invited to take part if they are not currently in the process of obtaining the Active School Flag. The normal process of the SLASF recruitment is for schools to make an application but this was suspended to allow time to develop the new model. Schools that were interested in carrying out the feasibility study contacted the Active Schools office and requested to pilot the second level programme. There were three schools that responded and accepted because they each have a strong well-being structure in place in their schools. This is a feasibility study with secondary outcomes on efficacy hence matched control schools (one girls only, one mixed and one mixed DEIS school) were recruited to take part in the survey component of the study. No reserve list was formed for this cohort but engagement of all three schools throughout the year to follow the feasibility and evaluate the SLASF process.

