### 2.5. Active School Flag Intervention

The SLASF feasibility model is co-designed by a SLASF steering group and staff, researchers of the University of Limerick and feedback from the three lead schools. The SLASF process is designed to be peer-led by a TY SLASF class, who will have the support of an SLASF coordinator, SLASF committee members, school staff and school management. The initiative challenges peers to find ways to encourage more students in their school to engage in school-based PA opportunities (year 1—SLASF certificate) and community-based PA opportunities (year 2—SLASF flag). During year 1 (Active School Flag certificate) the focus is on increasing participation in school-based PA opportunities. Year 2 (Active School Flag) is focused on community-based activities. 

Previously the SLASF was viewed as a physical education initiative. In order to generate greater whole-school engagement, the SLASF tasks are formatted to draw support for the SLASF TY team from school management and teachers across a variety of different subjects. The new format of the SLASF process complements two current key educational initiatives: The Well-Being Framework by the Irish National Council for Curriculum and Assessment, the School Self-Evaluation process by the Department of Education and Skills and a new initiative presently at draft stage: The Parent and Student Charter also by the Department of Education and Skills. Students working towards Gaisce the President’s Award can use their SLASF work to fulfil their Community or Personal Skill challenge requirement. Another benefit of SLASF is that it will link schools with the current national Healthy Ireland PA programmes and national youth charity events including: Get Ireland Walking—www.getirelandwalking.ieParkrun—www.parkrun.ieGet Ireland Swimming—www.swimireland.ie/get-swimmingSwim for a Mile Challenge—www.swimireland.ie/get-swimming/swim-for-a-mileDarkness into Light—www.darknessintolight.ieCycle Against Suicide—www.cycleagainstsuicide.com

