	ASF logbook entries	Notes that report barriers to completing actions that are not manageable
	PA audit	Low level of usage when compared with the beginning of the year

**Table 2 jfmk-04-00016-t002:** Aligning outcomes with measures.

SLASF Target Areas	Measures of Efficacy	Details
Physically educated	Self-efficacy in PA	Student survey
Physically active school community	Comprehensive Survey and focus groups	Survey item and discussions
Broad physical education	Whole-school survey and focus groups	List of physical education activities and discussions
Balanced physical education	Teacher scheme of work	Teacher records
More inclusiveness	Teacher scheme of work	Teacher records
Partnership with others to promote pa culture	TY logbook	Taster session from ASW
Active school week	TY logbook	Record of entries
Increased concentration	Harter scale	Student survey
Improved learning	Teachers perceptions	Student and teacher survey
Maintenance of discipline	Teacher records	Discipline records
Improved test results	Winter and summer test	Academic records
School enjoyment	Questionnaire	Student survey
Increase Daily PA	Accelerometers	Comprehensive Data
Reduced sitting time	Accelerometers	Comprehensive Data
Reduction in overweight and obesity	Self-report and anthropometric measures of height and weight	Comprehensive data

**Table 3 jfmk-04-00016-t003:** Battery of questionnaires.

Battery	Items	Response Scales	Psychometric Information
PA Screening measure	2 items on number of days in a week of at least 60 min of MVPA per day	0–7 days	Validity & Reliability [5,44]
PA opportunities	Modified items about local opportunities for PA to the context of schools instead of ‘residential area’	5 point scale, 1 = disagree a lot, 5 = agree a lot	Original items used from an interview guide.
The exercise self-efficacy scale for adolescents	10 items on confidence to participate in a variety of conditions	11 point sliding scale, 0 = not at all confident, 10 = very confident	Nigg & Courneya, 1999 [45]
PA peer support scale	4 items on the frequency of peers influence for PA	0 = never, 5 = every day	Prochaska et al., 2002 [46]
PA, plans, expectancy and intention	Modified 3 items on the planning, expectancy and intention to do PA in the coming week	1 = unlikely, 8 = likely	Hagger et al., 2001 [47]
Readiness for behaviour change	Single item to determine which stage of the transtheoretical model in terms of PA	Select one item of each stage of the transtheoretical model	Lee et al., 2001 [48]

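### The autumn-to-spring change in accelerometer activity and sitting has no control-school counterpart, so it cannot separate the programme from season or age trend and should be labelled descriptive

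*Protocol article*

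**What the plan says.** Section 2.8.1 sets two measurement waves for the comprehensive study: "The first time takes place in autumn 2018 and the second takes place six months later during the spring 2019". The device categories "are then compared at an individual level from pre- and post-test time points". Height, weight and grip strength are compared between waves too and are "used to control the differences in accelerometer data". The same section then says that follow-up data can test change through the intervention, and that models may take psychosocial variables into account. It mentions neither season nor a contrast between intervention and control schools.

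Table 2 places "Increase Daily PA" and "Reduced sitting time", both by accelerometer, under its efficacy column.

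Section 2.2.1 gives the reason for having controls: "This is a feasibility study with secondary outcomes on efficacy". The matched control schools "were recruited to take part in the survey component of the study". Table 4 nevertheless shows a comprehensive-study number for each control school.

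**The concern.** Every student with device data is in a programme school, was first measured in autumn and was measured again in spring. Wave, season, six months of ageing and exposure to the programme therefore coincide exactly. Body size and grip strength do not stand in for season, and a season term could not be added because it would be identical to the wave term.

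The authors recognised that an efficacy statement needs a comparator, since that is why control schools were recruited. As Section 2.2.1 reads, the comparator covers the surveys and leaves out the device outcomes. A seasonal rise could be reported as benefit, and a seasonal or age-related fall could hide benefit. Section 1 itself cites a mean decline in activity of 7% per year through adolescence.

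**Working it through.** **1. What the contrast estimates.** For a programme-school student, let D = spring value − autumn value. Then E(D) = programme + season + age. That is one equation with three unknowns. For a control-school student measured at the same times, E(D) = season + age. If those two terms are common to both groups, the difference in mean D is the programme effect. Without control device data the second equation is missing.

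**2. How large a shift would matter.** The article gives no power, SD or target effect for the device outcomes, so there is no figure to reproduce.
- From the article: 3 and 6 min/day of moderate-to-vigorous activity as effects of earlier peer-led programmes (Section 1.1); 100 + 150 + 150 = 400 comprehensive students in programme schools (Table 4).
- Assumed: two-sided alpha 0.05; SD of within-student change 15 to 25 min/day; 200 to 400 students with paired data; clustering ignored; programme effect zero.

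With a common shift s and SE = SD/√n, the probability of a significant paired test is Φ(s/SE − 1.96) + Φ(−s/SE − 1.96).

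For n = 400 and SD = 20, SE = 20/√400 = 1.0:

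| Shift s (min/day) | Probability of significance |
|---|---|
| 0 | 0.05 |
| 1 | 0.17 |
| 2 | 0.52 |
| 3 | Φ(1.04) = 0.85 |
| 6 | 1.00 |

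Over n = 200 to 400 and SD = 15 to 25, a 3-minute shift gives 0.40 to 0.98 and a 6-minute shift gives 0.92 to 1.00.

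**3. Age trend.** A decline of 7% per year is 1 − √0.93 = 3.6% over six months. On an assumed mean of 40 to 60 min/day that is 1.4 to 2.1 min/day downward. It is smaller than the 3-minute benchmark but not negligible beside it.

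**4. What a controlled contrast can deliver.** Table 4 gives 123 + 121 + 88 = 332 comprehensive students in control schools. In units of the SD of change:
- Ignoring clustering, SE = √(1/400 + 1/332) = 0.074.
- With an assumed school-level share of variance ρ and equal school weights, each school contributes ρ + (1 − ρ)/n. Each group's contributions are summed and divided by 3² = 9, and the two groups are added. The SE is 0.111 for ρ = 0.01 and 0.197 for ρ = 0.05.
- Six schools in two groups leave 4 degrees of freedom (t = 2.776). The 95% half-width is 2.776 × 0.111 = 0.31 to 2.776 × 0.197 = 0.55 SD.

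The contrast removes a common seasonal shift, but it is an estimate with wide uncertainty and not a powered test. These figures assume that all expected students have data at both waves.

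**The case against.** The strongest reply is that this is a feasibility study. Section 1.4 lists accelerometry among the things whose collection is being tried out, and the decision rules sit in Table 1. A reader might infer that a misleading device result would drive the choice to stop, revise or go to a randomised trial. The documents do not support that. The limited-efficacy rows use the comprehensive surveys, the logbook and the activity audit. The survey row even sets a decline against differences between year cohorts at baseline, which is a form of age benchmark. This part of the reply stands and limits the consequence.

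The absence of control devices is also less certain than Section 2.2.1 suggests. Table 4 gives comprehensive numbers for schools D, E and F, and Section 2.3 ties the comprehensive study to accelerometers. The reading that fits both is that controls complete the comprehensive survey only, but the article does not say so.

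A reader might also hold that a daily outcome is mismatched to year 1, where "the focus is on increasing participation in school-based PA opportunities", and that out-of-school change could be subtracted as a seasonal comparator. That goes too far. The certificate tasks in Sections 2.5 and 2.5.2 include community mapping, a community event and an Active School Week that points families to local opportunities. Out-of-school time is therefore partly targeted, and subtracting it could remove real benefit. Nor would a school-hours window remove season, because outdoor lunchtime activity can vary with season too.

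Finally, autumn and spring visits six months apart might lie at similar distances from midwinter, so the shift could be small. That is possible. The plan offers no means of knowing.

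**Conclusion.** The concern holds for the secondary device outcomes. As described, the autumn-to-spring change in accelerometer activity and sitting cannot be attributed to the programme, although Table 2 and Section 2.8.1 present it as evidence of efficacy. The primary acceptability objective and the Table 1 criteria are not affected through this route.

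The confounding follows from the stated timing and the stated role of the control schools, and needs no assumption beyond reading Section 2.2.1 at face value. Its size does rest on assumptions. Neither the magnitude nor the sign of a seasonal shift is in the documents, so the 0.40 to 0.98 range for a 3-minute shift shows sensitivity and does not predict what will happen.

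**What to change.** Revise Section 2.8.1 as follows.

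1. Make the intervention-versus-control difference in change on the 60-minute screening items (Table 3) the efficacy contrast for physical activity. Report it with an interval that reflects three schools per group. This assumes that control students complete those items at both waves, which should be stated.
2. Label the autumn-to-spring device change as descriptive and not as evidence of programme effect.
3. Optionally, report device change separately for school hours and out-of-school time, without subtracting one from the other. This presumes time-stamped recordings that include school days.
4. Reconcile Section 2.2.1 with Table 4 on whether control-school students wear devices. If they do, apply the same difference-in-change contrast to the device outcomes.

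Items 1, 2 and 4 are changes of wording and analysis on data already planned. Item 3 adds one processing step. The cost is a weaker efficacy statement from the device data, a controlled contrast that relies on self-report, and an interval that will be wide.
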